## Abstract

**Background:**

Clean intermittent self-catheterisation is an important management option for people who cannot empty their bladder effectively. Recurrent urinary tract infections are common in these patients. Data from recent studies suggest that antibiotic prophylaxis may be beneficial in reducing infection risk, but the effectiveness of this intervention remains uncertain.

**Methods/design:**

This is a 52-site, patient randomised superiority trial set in routine care comparing an experimental strategy of once daily antibiotic prophylaxis for 12 months against a control strategy of no prophylaxis in people who carry out self-catheterisation and suffer recurrent urinary tract infections. The primary outcome is number of urinary tract infections during a 12-month treatment period. Both groups will otherwise receive usual care including on demand treatment courses of antibiotics for urinary tract infection. Participants and their clinicians will not be blinded to the allocated intervention, but central trial staff managing and analysing trial data will, as far as possible, be unaware of participant allocation. The analysis will follow intention-to-treat principles.

**Discussion:**

This trial was commissioned and funded by the United Kingdom National Health Service following prioritisation of the research question by the National Institute for Health and Care Excellence.

**Trial registration:**

ISRCTN67145101 EUDRACT2013-002556-32. Registered on 25 October 2013.

**Electronic supplementary material:**

The online version of this article (doi:10.1186/s13063-016-1389-y) contains supplementary material, which is available to authorized users.

## Background

Clean intermittent self-catheterisation (CISC) is a frequently used intervention for people who cannot empty their bladder effectively due to bladder outlet obstruction or failure of bladder muscle contraction which may be associated with neurological disease [1]. Patients needing CISC are taught how to insert a catheter, drain the bladder and then remove the catheter [2]. Single-use disposable catheters, typically with a hydrophilic coating, are predominantly used in the UK [3].

There are no accurate prevalence data for CISC use in the UK. The National Health Service (NHS) England prescription database recorded 47 million CISC catheter prescriptions in 2010 at a cost of £64 million [4]. If we assume each individual uses an average of 25 catheters per week, this suggests that there are about 36,000 CISC users in England and perhaps 43,000 in the UK as a whole. This estimate is in agreement with a primary care-based estimate which found a prevalence of approximately 7–8 per 10,000 adults, suggesting an approximate total of 43,000–49,000 adults in the UK ([name], personal communication, August 2011).

Recurrent urinary tract infection (UTI) is the commonest adverse event experienced by CISC users affecting between 12–88 % of studied cohorts [5]. Differentiation between asymptomatic bacteriuria, which would not normally be treated, and symptomatic UTI in these studies is difficult. One estimate suggests that 50 % of users have persistent bacteriuria and at least 25 % suffer two or more symptomatic UTI episodes per year [6]. Conservatively this suggests that up to 10,000 CISC users in the UK suffer recurrent UTI, the target population for this trial. Neurological disease, female sex, young age and high bladder volumes are associated with higher prevalence of UTI [1]. *Escherichia coli* (*E. coli*) is the causative bacterium in 60–70 % of cases [6]. Most episodes are associated with transient symptoms such as lower abdominal pain, urethral pain and flu-like symptoms; occasionally systemic upset can occur with fever and loin pain. Those with reduced bladder sensation may alternatively complain of cloudy urine, increased odour and incontinence [7]. Recurrent UTI is distressing and an additional burden for patients with underlying neurological disease and functional disability [5]. For some there is a risk of renal damage in the longer term [7] or significant sepsis requiring intensive care and potential mortality.

A number of simple interventions have been trialled to reduce UTI risk for CISC users, including single-use and hydrophilic catheters and antiseptics, but none showed efficacy [2]. A randomised controlled trial (RCT) reported a benefit of hydrophilic catheters for patients with spinal cord injury during initial hospitalisation [8]. The need for strategies to reduce the prevalence of UTI in this population has been emphasised by reports in the UK from the James Lind Alliance and the National Institute for Health and Care Excellence (NICE) [9, 10].

Once daily low-dose antibiotic prophylaxis is effective for women without bladder emptying problems who suffer simple recurrent UTI. Systematic review and meta-analysis of trials in this patient group showed a relative risk for UTI (95 % confidence interval, CI) against placebo of 0.15 (0.08–0.28) [11]. Adverse events in trials using nitrofurantoin, trimethoprim or cephalexin were mild and rarely associated with withdrawal, but were more frequent in the antibiotic group with a relative risk (95 % CI) of 1.78 (1.06–3.0); gastro-intestinal upset, skin rash and vaginal candidiasis predominated. Nitrofurantoin appeared more effective than trimethoprim but resulted in more withdrawals. These two drugs together with cephalexin are recommended and licensed for this purpose in the UK [12]. There were no reports of serious adverse effects such as neuropathy or pulmonary fibrosis in the nitrofurantoin arms of randomised studies included in the Cochrane review, but an observation study of prophylactic nitrofurantoin noted one episode of possible neuropathy in 219 patients over 12 months’ use [13].

Current evidence for effectiveness of antibiotic prophylaxis by CISC users, the focus for this trial, has been summarised by a Cochrane review updated to September 2011 [14]. We were unable to identify any further published or ongoing trials from that date up to December 2015. The review found six RCTs involving adults (four trials) or children (three trials) performing CISC for neurological bladder dysfunction with a total of 406 participants. Five had placebo as a comparator with either a crossover or parallel group design, and three each used clinical or microbiological definition for UTI outcome; the latest report was 2011. Two of the crossover trials had a duration of 3 months for each intervention without washout whilst one had a duration of 5 months for each intervention and a 1-month washout period. The prophylactic agents used were trimethoprim-sulfamethoxazole (two trials) and nitrofurantoin (four trials) and a variety of agents (one trial). Participant attrition after randomisation ranged from 2–35 %. One trial using the outcome of clinically defined symptomatic UTI found a relative incidence rate (95 % CI) of 0.50 (0.17–1.44) in favour of antibiotic prophylaxis whilst another trial found no difference. For the outcome of microbiologically proven symptomatic UTI, one trial found a relative risk of 0.78 (0.62–0.79) in favour of prophylaxis. Evidence from four trials showed an overall relative incidence rate (95 % CI) for bacteriuria of 0.61 (0.44–0.87) in favour of prophylaxis. The review authors concluded that, although results were promising, there was a lack of unequivocal evidence for effectiveness of antibiotic prophylaxis for CISC users, agreeing with a previous review [15]. Recommendations for future trials were as follows:Use incidence of symptomatic UTI as the primary outcomeMeasure antibiotic resistanceControl for factors increasing UTI risk: sex, frequency of catheterisation, neurological cause, frequency of previous UTI, prior use of antibiotic prophylaxis

None of these trials found any excess harms in the prophylaxis groups, but ecological changes in pathogens were not studied. These results and the need for further trials have been highlighted in a further narrative review [16].

In a large RCT of antibiotic prophylaxis of recurrent UTI in women with normal voiding, it was found that faecal and urinary carriage of resistant *E. coli* was increased from 40 % to 80 % by use of trimethoprim-sulfamethoxazole once daily prophylaxis but that this returned to baseline 3 months after discontinuing of the antibiotic prophylactic therapy [17]. There remains public health concern regarding the empiric prophylactic widespread use of antibiotics given the rapid emergence of resistant strains of bacteria, including *E. coli*. Antimicrobial stewardship, including the appropriate use of antimicrobial prophylaxis, has become a priority.

This background has led us to design a robust pragmatic trial to determine whether the apparent benefit of antibiotic prophylaxis seen in small trials amongst specific groups of CISC users is also seen in a routine care setting and whether the benefits are worthwhile in terms of harms. The estimates of prevalence, effectiveness and harms have allowed us to power the trial conservatively based on what we consider to be a minimum important difference from clinician, patient and economic perspectives.

## Methods/design

This is a 52-site, pragmatic, patient randomised superiority trial designed to answer the question: In people carrying out CISC who suffer recurrent UTI does an experimental strategy of once daily antibiotic prophylaxis reduce the rate of symptomatic UTI compared to a control strategy of no prophylaxis? Both groups will otherwise receive usual care, including on demand discrete courses of antibiotic treatment for UTI. The trial will be set in both primary and secondary National Health Service (NHS) care in the UK. Participants and their clinicians will not be blinded to the allocated intervention, but central trial staff managing and analysing trial data will, as far as possible, be unaware of participant allocation. We will also assess participant perception of benefit: firstly, by completion of a treatment satisfaction questionnaire on exit; secondly, by qualitative analysis of semi-structured interviews on trial completion exploring the views and attitudes of a purposive sample of participants towards the trial intervention. The primary economic analysis will assess the cost per UTI avoided, but we will also perform a cost-utility analysis and a contingent valuation study. Bacterial ecological change will be assessed by comparing changes in resistance patterns of *E. coli* in participant urine and perianal swab samples. We have formulated a recruitment plan to progressively build to a target of 372 participants over 28 months. Outcomes will be collected over 12 months for each participant and analysed at trial termination according to intention-to-treat principles.

The null hypothesis is that the effectiveness and cost-effectiveness of a strategy of prophylactic antibiotic are not superior to those for no prophylaxis over 12 months.

The anticipated trial flow for participants is illustrated in Fig. 1.

**Fig. 1 Fig1:**
[figure not shown]
CONSORT diagram showing flow of trial participants through the trial

### Objectives

#### Primary objectives

The primary objectives are to:Determine the relative impact of each intervention on incidence of UTI over 12 monthsDetermine the incremental cost per symptomatic UTI avoided

#### Secondary objectives

The secondary objectives are as follows:Clinical○ Determine the relative effect on quality of life (QoL) amongst trial participants○ Measure overall satisfaction with prophylactic antibiotic treatment○ Assess participants’ perception of benefit at 12 months using qualitative methodology○ Record adverse effects related to both prophylaxis and treatment antibiotic use○ Determine relative rates of hospitalisation because of UTI○ Measure difference in renal function by estimated glomerular filtration rate (eGFR) at 12 months○ Determine rates of asymptomatic bacteriuria at 12 months○ Assess ecological change in *E. coli* isolated from urine and perianal swabsEconomic○ Measure incremental cost per QALY gained through repeated completion of SF-36○ Assess participants’ willingness to pay to avoid a UTI by contingent valuation at end of trial participation and incorporate these data in the economic evaluation using a cost-benefit framework.

### Primary outcome measures

The primary outcome is difference in incidence of symptomatic UTI during the 12-month observation period. Symptomatic UTI will be defined on fulfilment of two criteria. The first will be the presence of at least one patient-reported or clinician-recorded symptom from a predefined list encompassing the recommendations of the British Infection Association (BIA) [18], the Centers for Disease Control and Prevention (CDC) [19] and spinal cord injury UTI consensus statement [8] comprising: fever (being hot and sweaty); shivers; cloudy urine; smelly urine; visible blood in urine; new or increased urinary leakage (incontinence); lower abdominal pain; having to catheterise more often; having to rush to catheterise; pain when one puts the catheter in; feeling generally unwell (‘fluey’); stiffness or worsening stiffness (spasticity) of arms and legs. The second criterion is taking a discrete treatment course of antibiotics prescribed by a clinician or as part of a patient-initiated self-start policy. Occurrence of symptomatic UTI with prescription of a treatment course of antibiotic will be captured by:Participant log with report alert sent by participant to trial staff.Contact with each participant at least every 3 months by local trial staff and more frequently if required to aid participant recording of UTI episodes.Response to specific enquiry in participant questionnaire completed at 3, 6, 9 and 12 months.End of trial review of hospital and primary care record at 12 months.For any identified treatment course of antibiotics for UTI the participant will be asked to complete a multiple choice description of symptoms that precipitated the request for antibiotic treatment.

To ensure consistent attribution we will set a hierarchy of evidence on which to base the primary outcome. First will be participant-reported episodes of symptoms that they considered to be due to UTI and for which they obtained treatment with an appropriate antibiotic. If, in discussion with the participant, there is uncertainty as to whether an antibiotic was taken or if the stated antibiotic was not of a type normally used for UTI, the relevant general practitioner (GP) or hospital record will be checked for confirmation that a prescription for an antibiotic to treat UTI was issued (including previous prescriptions for self-start therapy). Where no antibiotic prescription was found in the record, we will ask the participant to confirm the origin of the prescription. If we were unable to confirm issuing of either a single course or self-start supply of antibiotics, then the primary outcome will not be fulfilled. The second type of event will be the identification of a prescription of an antibiotic during the planned 3-monthly interrogation of healthcare records without a participant report of a UTI. In this case the participant will be contacted to check that they did take a treatment course of antibiotics at that time and to assess their symptom status. If the participant had no recollection of the antibiotic course, or if there was no evidence from the participant or healthcare records of any change to baseline urinary symptoms, then the episode will be judged not to have fulfilled the primary outcome.

#### Primary economic outcome

The primary economic outcome is the incremental cost per symptomatic UTI avoided. It includes the following costs associated with the prophylaxis and no prophylaxis strategies including cost of harms:○ Treatment costs of drugs and healthcare services from standard NHS sources such as the British National Formulary (BNF) and published tariffs from NHS reference costs○ Health resource utilisation questionnaire at baseline and at 6 and 12 months○ Patient costs from a time and travel questionnaire as part of the 12 months exit assessment

### Secondary outcome measures

Secondary outcome measures will be collected as additional criteria to the primary outcome from inspection of participant healthcare records, by participant questionnaire or by clinical test performed at specific time points. The following are also included.The rate of UTI will also be alternatively defined as the *incident density rate*; the number of UTIs suffered during the observation period minus days spent taking treatment courses of antibiotics active against urinary tract organisms.*Febrile UTI* defined as the primary outcome plus presence of a recorded fever of more than 38 °C:○ Confirmed by inspection of primary or secondary healthcare record by research staff.*Microbiologically confirmed symptomatic UTI* defined as the primary outcome plus positive urine culture:^1^○ Participants will provide an intermittent catheter specimen of urine for local analysis as requested by the treating clinician. This will be analysed according to clinician decision by the local microbiology using the local standard operating procedure (SOP). We will also ask the participant to send a urine specimen using provided safe packaging to the central microbiology trial laboratory in the Newcastle upon Tyne Hospitals NHS Foundation Trust each time they consider they have symptoms suggestive of UTI and intend to commence a course of antibiotic treatment. This will be analysed and cultured on receipt and the result used for trial outcome purposes but not for patient care.*Antibiotic prescription for asymptomatic UTI* without participant-reported or clinician recorded evidence of symptom change.*Asymptomatic bacteriuria* defined as a positive urine culture in the absence of symptoms.○ Participants will be asked to send a urine sample to the central laboratory at baseline prior to randomisation and during asymptomatic periods in months 3, 6, 9 and 12 of their trial participation. They will also be separately consented to provide a urine sample 6 months after completion of trial (18-month time point).*Hospitalisation due to UTI* defined as an unplanned visit to hospital for treatment of a UTI which required at least one overnight stay in hospital.○ Collected from healthcare record review and checked from participant report or enquiry.*Participant perception of benefit.*○ We will record and analyse semi-structured interviews with up to 30 participants purposively sampled from both trial arms on completion of their 12-month trial period.*Overall satisfaction with allocated treatment strategy.*○ Participants will complete the treatment satisfaction questionnaire for medication at 12 months as part of their completion of trial questionnaire [20].*Generic health-related quality of life.*○ Participant completion of the SF-36 1-week recall questionnaire at baseline, 3, 6, 9 and 12 months and within the first 2 days of each episode of symptomatic antibiotic-treated UTI [21].

#### Adverse effects (harms)

The adverse effects are as follows.*Adverse effects of antibiotic therapy*○ During antibiotic prophylaxis use▪ Collected by participation checklist completed at 3, 6, 9 and 12 months▪ Recording of relevant data from primary and secondary care records at 12 months○ During treatment antibiotic use▪ Collected as part of participant log during episode of antibiotic-treated UTI▪ Recording of relevant data from primary and secondary care records at 12 months*Change in renal function* defined as estimated creatinine clearance measured by serum creatinine blood test at baseline before randomisation and during an asymptomatic period in month 12*Change in liver function* defined as clinically significant change in liver function indices measured by serum liver function tests (LFTs) at baseline and at 12 months*Bacterial ecological changes* to type and resistance patterns of *E. coli* isolated from urine specimens and perianal swabs analysed at the central laboratory at baseline prior to randomisation and at 3, 6, 9 and 12 months after randomisation and from surveillance of other urine specimens submitted to the central laboratory. Participants will also be separately consented to provide a urine specimen and perianal swab together with an antibiotic use questionnaire 6 months after completion of trial (18-month time point).

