#### One month (after randomisation and repeated if required: telephone)

A member of the trial staff will contact the participant regarding general concerns, understanding of trial documentation and tolerance of prophylactic antibiotic agent (if allocated).

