#### Three, six and nine months after randomisation (telephone/postal or face-to-face - according to individual participant circumstance)

The participant will complete trial outcome questionnaires and reports of any UTI and associated symptoms as well as adverse effects. Adherence to prophylaxis will be checked if allocated to this arm of the trial. During this time participants will complete the SF-36 and healthcare resource use questionnaire. They will send in a urine specimen during an asymptomatic period to the central laboratory for analysis and storage.

The local research staff will search clinical records (secondary and primary care) for episodes of UTI, episodes of UTI which are associated with fever greater than 38 °C, antibiotic prescription for UTI prophylaxis and other reasons, episodes of hospitalisation for UTI and other ill health and results of local laboratory urine culture.

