### Study adherence and withdrawal

#### Assessment of adherence

Outcome data will be collected remotely whenever feasible by participant completion of postal or secure web-based questionnaires. This will be supplemented by e-mail or text alerts to participants notifying the need to complete questionnaires with additionally up to two reminders in these formats for non-responders. Local research staff will make use of planned routine clinical visits, whether for the underlying health condition or urinary tract monitoring, to check completion of trial documentation and collect clinical outcome information such as urine and perianal swab specimens. Participants allocated to prophylaxis will be contacted after 1 month to assess tolerability and if necessary allow change to alternative agent with re-checking of tolerability after a further month. We will assess adherence to the allocated arm (prophylaxis or no prophylaxis) by 3-monthly contact with the participant to check tolerability and surveillance of their primary healthcare record to record issuing of relevant prescriptions and consultations involving discussion of UTI treatment. We will contact participants more frequently if they need assistance to complete trial documents, particularly the UTI log.

All information will be recorded in the relevant CRF. If we do detect change from allocation, we will explore and record the reasons for this with the participant and the relevant clinician. Wherever possible these participants will remain on study and continue collection of planned outcome information. Trial literature will emphasise the need to adhere to the allocated strategy during the 12-month trial period if possible and will record any deviation. Multiple switching between prophylactic agents will be allowed. Previous studies suggest that this will affect approximately 12 % of participants [26], although a higher rate was seen in children (48 %) [27]. The trial statistician will monitor attrition rate against our anticipated maximum of 15 % and report to the TSC and DMC.

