A number of additional secondary analyses will also be undertaken to examine the secondary outcome variables. Febrile and microbiologically confirmed UTI, asymptomatic bacteriuria and hospitalisation due to UTI will be analysed in a manner analogous to that for the primary outcome. Analyses of other outcomes will use similar regression or analysis of variance/covariance-based approaches as described above to compare between treatment groups while allowing for the effects of covariates. Baseline measures would be included in the analysis, either considered as possible covariates or by exploring changes in outcome measures from baseline. Analysis will be carried out primarily on an intention-to-treat basis, although other exploratory analyses such as per-protocol may also be considered. Data will be analysed at the end of the study; there are no planned interim analyses. Safety data will be regularly and frequently reviewed but will not be subjected to statistical analysis. Data with missing observations due to loss to follow-up will be examined to determine both the extent of the missing data and whether they are missing at random or are informative. If data are missing to a sufficient extent, the use of appropriate multiple imputation techniques will be considered.

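### Antibiotic adverse effects are defined by exposure and safety data are excluded from statistical analysis, so the plan as written gives on-drug counts and no comparison by randomised arm

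*Protocol article*

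**What the plan says.** The section Adverse effects (harms), which sits under the secondary outcome measures, splits the adverse effects of antibiotic therapy in two. The first category is "During antibiotic prophylaxis use▪ Collected by participation checklist completed at 3, 6, 9 and 12 months". The second, for treatment courses, is "Collected as part of participant log during episode of antibiotic-treated UTI". Both are supplemented from care records at 12 months. The matching secondary objective is to "Record adverse effects related to both prophylaxis and treatment antibiotic use"; it does not mention a comparison.

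The visit descriptions are wider. At 3, 6 and 9 months, "The participant will complete trial outcome questionnaires and reports of any UTI and associated symptoms as well as adverse effects". The 12-month section is similar, and in both places only the adherence check is confined to those allocated prophylaxis. Table 1 marks adverse events at 3, 6, 9 and 12 months and at each UTI, with no restriction by arm.

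The 1-month call is described in more than one way. Its own section says "A member of the trial staff will contact the participant regarding general concerns, understanding of trial documentation", with a tolerance question for those on prophylaxis. Assessment of adherence says "Participants allocated to prophylaxis will be contacted after 1 month to assess tolerability and if necessary allow change to alternative agent", with a re-check a month later. Antibiotic prophylaxis (experimental) also presents the call as a tolerability review and adds further calls if needed. Table 1 has no 1-month column.

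On analysis, the Statistical analysis section says "Safety data will be regularly and frequently reviewed but will not be subjected to statistical analysis". The Background gives as part of the trial's purpose to learn "whether the benefits are worthwhile in terms of harms".

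**The concern.** A category defined by being on prophylaxis has no counterpart in a no-prophylaxis arm. Its count mixes drug effects with complaints that would have occurred anyway, and gastro-intestinal upset, rash and candidiasis (the effects named in the Background) also occur without prophylaxis. Only a comparison by randomised arm separates the two. The outcome definition does not ask for that comparison, and the analysis sentence, as worded, rules it out.

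The trial is unblinded and these effects are largely participant-reported. If the prophylaxis arm is asked about tolerance at additional contacts and those reports enter the count, part of any difference between arms would reflect how often people were asked.

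The stake is the harm side of the benefit-harm judgement. The primary result would come with a rate ratio and an interval, and the adverse effects with a list.

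**Working it through.** **Step 1: what each section provides.**

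| Section | Who is covered | Allows a by-arm comparison? |
|---|---|---|
| Adverse effects (harms), first category | Those taking prophylaxis | No, there is no control counterpart |
| Adverse effects (harms), second category | Anyone on a treatment course, either arm | Only if counted by arm |
| Visits at 3, 6, 9 and 12 months | All participants | Yes |
| Table 1, adverse events row | All participants | Yes |
| Renal function, liver function, *E. coli* resistance | All participants, scheduled times | Yes |
| Statistical analysis, safety sentence | Safety data, without limitation | Excludes analysis as worded |
| Statistical analysis, other outcomes | Compared between groups by regression or covariance methods | Would include harms, which are listed as secondary outcomes |

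The data collection supports an arm comparison; the definition and the safety sentence do not use it. The last two rows also disagree with each other.

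**Step 2: origin of the 158 per arm.** The protocol gives no figure for harms, so the only stated input available is the primary sample size. For the Poisson rate test, two-sided 5% and 90% power:

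n = (1.960 + 1.282)² × (3 + 2.4) / (3 − 2.4)² = 157.6, so 158 per arm; 316 / 0.85 = 372.

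Both match the stated figures.

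**Step 3: precision of a by-arm comparison.** Inputs: n = 158 completers per arm (Sample size calculation) and relative risk 1.78 (Background, from women without bladder emptying problems). The control risk p₁ is an assumption, because the protocol gives none; p₂ = 1.78 p₁.

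- SE of log RR = √[(1 − p₁)/(n p₁) + (1 − p₂)/(n p₂)]
- SE of risk difference = √[p₁(1 − p₁)/n + p₂(1 − p₂)/n]

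For p₁ = 0.15: p₂ = 0.267. SE(log RR) = √(0.85/23.7 + 0.733/42.19) = 0.231. The interval is 1.78 × exp(±1.96 × 0.231), or 1.13 to 2.80.

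| Assumed control risk | Prophylaxis risk | 95% CI for RR | Risk difference ± half-width (points) |
|---|---|---|---|
| 5% | 8.9% | 0.77 to 4.14 | 3.9 ± 5.6 |
| 10% | 17.8% | 1.00 to 3.16 | 7.8 ± 7.6 |
| 15% | 26.7% | 1.13 to 2.80 | 11.7 ± 8.9 |
| 20% | 35.6% | 1.22 to 2.59 | 15.6 ± 9.7 |
| 30% | 53.4% | 1.35 to 2.35 | 23.4 ± 10.6 |

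**Step 4: effect of unequal questioning.** If events are captured c times as readily in the prophylaxis arm, observed RR = true RR × c. For an assumed c of 1.10 to 1.50, a true RR of 1.00 would appear as 1.10 to 1.50. The protocol does not allow c to be estimated. Using only the contacts common to both arms removes this source.

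**The case against.** The strongest reply is that the information is there. Adverse effects are reported by all participants every three months, and renal, liver and resistance outcomes are scheduled in both arms. This stands, and it defeats a stronger reading that a reader might reach: that the excess harm of prophylaxis cannot be estimated. It can be, from data the protocol already plans to collect.

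A reader might also infer that harms avoided through fewer treatment courses are ignored. They are not. Treatment-course effects are recorded in both arms, and fewer of them under prophylaxis would be part of the strategy's effect.

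Nor should one divide by 1.78 to say what share of on-drug events is background. That relative risk comes from a different population, and the Background reports no excess harms in the prophylaxis groups of the trials in people who self-catheterise. The calculation would matter only if control data were absent.

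On contacts, the section on the 1-month call addresses every participant, and three-monthly contact covers both arms. What differs is the tolerance question and some conditional calls. The asymmetry is therefore modest.

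On analysis, the safety sentence follows directly after the statement that no interim analyses are planned, so it may be meant for ongoing review. Detailed harm analyses also commonly sit in the statistical analysis plan, which is not shown, and their absence here is no fault. But the sentence is not limited to ongoing review. It states a rule, and an analysis plan that compared harms would contradict it as written.

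**Conclusion.** The point holds in this form: the outcome definition and the safety sentence together give on-drug counts where the aim stated in the Background needs a comparison by randomised arm. It is a fault of definition and analysis wording; the planned data collection is adequate for the comparison. It concerns the adverse effects of antibiotic therapy. The renal, liver and resistance outcomes are not defined by exposure and are affected only if the safety sentence is read to cover them.

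No stated number is wrong. The size of the loss depends on the control-arm risk, which is unknown. With RR 1.78 and 158 per arm, the comparison would be informative at an assumed 15% risk (1.13 to 2.80) and weak at 5% (0.77 to 4.14). Those intervals rest on a relative risk borrowed from another population and on complete data for 158 per arm. Whether unequal contact would inflate the count, and by how much, cannot be determined from the protocol.

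**What to change.** 1. In Adverse effects (harms), define the outcome as the number of participants with adverse effects, and the number of effects, from the same 3-monthly checklist in both arms, compared by randomised arm over 12 months. Keep the split between prophylaxis and treatment courses as description.
2. In Statistical analysis, limit the no-analysis sentence to ongoing review during the trial. State that final harms are compared by randomised arm with risk differences and 95% confidence intervals.
3. Reconcile Antibiotic prophylaxis (experimental), the one-month section and Assessment of adherence on who receives the 1-month call. Base the between-arm comparison only on the contacts common to both arms (3, 6, 9 and 12 months), so that extra tolerability calls do not raise the count in one arm.

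The cost is a change of wording and a little more analysis. No new visit is needed. The limitation is precision: if the control-arm risk is low, the interval will be wide and should be reported as such.
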